#### Outcomes

Our primary outcomes include: (1) feasibility of intervention, and (2) acceptability of intervention. Secondary outcomes include: (1) change in number of self-reported CC per day based on daily reports that are provided for 84 days post-baseline and (2) change in pulmonary symptoms based on CAT scores at 12 weeks.

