#### Intervention

##### Intervention arm: EC + counseling

At baseline, intervention arm participants will be provided with a kit containing approximately one month’s supply of EC. If the initial supply does not cover the full month’s use, participants will be able to request an additional supply or change of flavors. A new supply of EC will be distributed regularly during each study visit and as needed for 12 weeks. Participants will be asked to provide regular text messaging check-in reports 4 times over the course of each day to report CC and EC use.

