##### Behavioral counseling

At baseline, all participants will receive a 30-min counseling session delivered by telephone from a counselor trained in motivational interviewing and smoking cessation treatment tailored to the participant’s designated EC or NRT arm. The proposed counseling program has been shown to be acceptable and effective for achieving abstinence in a previous smoking cessation program [57]. Counseling sessions will be similar between the two arms and use the same counseling techniques. Counseling will be provided by a licensed mental health counselor with extensive experience in the field of health psychology and behavioral health research. The same counselor will contact each participant by telephone at 2 weeks and 1 and 2 months to deliver additional 10–15 min counseling sessions, for a total of 4 counseling sessions. For this pilot, a single counselor is expected to complete sessions for all participants, however if additional counselors are used they will be trained to ensure consistent intervention delivery and will evenly split participants between arms.

The purpose of the counseling is to: (1) discuss the impact of continued smoking on their COPD; (2) deliver motivational enhancement for switching from CC to EC (EC arm) or smoking cessation (NRT arm); (3) promote self-efficacy; and (4) inform participants about EC and NRT use. The counseling protocol will be characterized by (1) Motivational enhancement – We will include motivational enhancement in the initial counseling and each of the telephone calls to increase patient motivation to switch from CC to EC or quit smoking; (2) Problem-solving therapy—this approach—endorsed by the national smoking cessation guidelines [32]—will be adapted to focus on helping the smoker identify and solve challenges in switching from CC to EC or quitting smoking.

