##### Tobacco product use

CC and EC/NRT product use will be measured as part of a text messaging EMA protocol serving as a smoking diary that incorporates a behavioral “coverage” strategy, designed to maximize the odds that all behavioral events of interest are documented accurately and minimize missing data [44]. Daily recording of product use via EMA allows for measurement of dual use of products and observation of switching patterns. This also provides a measure of CPD over time. After the baseline assessment, participants will be asked to record daily nicotine use by responding to text message prompts. The coverage design prompts participants to provide regular, and very brief, check-in reports via text message over the course of each day, wherein they are asked to report use of EC or NRT based on their study arm and CC over the window of time elapsed since their last report (~ 4 h). One item measures of CC craving and EC/CC satisfaction are collected at each report.

Combined in succession, these coverage reports produce near-complete and consistent use reports over relatively extended periods, partly because they require only seconds for subjects to complete. Text message smoking diary prompts will be automated using SlickText Workflows software and their associated text distribution platform. Frequency of text message prompts will be four per day, corresponding to time windows breaking the day into “Early/Lunch/Afternoon/Evening” periods. There is minimal burden since each data collection instance takes an average of one minute to complete each session. Participants will receive a text message prompt asking them to complete an assessment (Fig. 2). The system is programmed to prevent skipping items or entering out-of-range values. Data is continuously synchronized with a secure web-based HIPAA compliant server. All entries will be time- and date-stamped. The system will record the time it took the participant to respond (response delay), time to completion, and missed prompts. All participants will be instructed how to document their daily tobacco use.

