#### Statistical methods

Before addressing the study aims, data will be summarized numerically using descriptive statistics. Comparison of the baseline characteristics between the study arms will be performed using chi-square tests for categorical data and t-tests or nonparametric tests for ordinal or continuous data. Preliminary analyses will investigate possible differences on the primary outcomes by gender and race/ethnicity. If differences appear, race/ethnicity and/or gender will be entered as covariates. Exploratory analyses will be conducted where appropriate to better understand the findings. Otherwise, analyses will collapse across race/ethnicity and gender. All data will be presented in aggregate and de-identified prior to publication.

Feasibility and acceptability will be summarized using descriptive statistics. Simple logistic regressions, including ordinal and multinomial models, will be used to compare the characteristics of participants reporting high and low acceptability. We will evaluate the impact of EC vs. NRT on the reduction in self-reported CPD and CAT Score, at 12 and 24 week follow-up assessments, with and without the addition of covariates. CPD at baseline and 12 weeks will be extracted from EMA data, while the 24-week follow-up will be self-report from the telephone survey. The impact of EC vs. NRT on change in CPD and CAT Score will be estimated using a Poisson or negative binomial regression model [47] with follow-up CPD/CAT Score regressed on baseline CPD/CAT Score and an indicator variable of study condition (EC vs. NRT).

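### Baseline CPD is to come from the text diary, which starts only after allocation, so the baseline covariate in the CPD model is a post-randomisation measurement

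*Protocol article*

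**What the plan says.** The Statistical methods section fixes the source of the CPD data: "CPD at baseline and 12 weeks will be extracted from EMA data, while the 24-week follow-up will be self-report from the telephone survey". The model regresses follow-up CPD on baseline CPD and an arm indicator, using Poisson or negative binomial regression, at 12 and 24 weeks.

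Other sections fix when the diary runs:

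- Tobacco product use: "After the baseline assessment, participants will be asked to record daily nicotine use by responding to text message prompts". The prompts ask participants to "report use of EC or NRT based on their study arm and CC over the window of time elapsed since their last report", so the arm is known when they are sent.
- Outcomes: the secondary outcome is "change in number of self-reported CC per day based on daily reports that are provided for 84 days post-baseline".
- Trial design: randomisation follows completion of the baseline survey, and the diary covers the 12 weeks of participation.
- Intervention arm: "At baseline, intervention arm participants will be provided with a kit".
- Behavioral counseling: "At baseline, all participants will receive a 30-min counseling session", tailored to the assigned arm.
- Randomization: participants know their allocation.

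No section describes diary days before allocation.

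**The concern.** A baseline covariate is safe to adjust for because treatment cannot have influenced it. A diary value collected after an unblinded allocation, arm-specific counselling and product supply lacks that protection. If CPD has already moved apart between the arms when this value is taken, conditioning on it credits part of the treatment effect to the covariate. If smoking has already fallen in either arm, the reduction measured from that value is too small.

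The comparison affected is aim 2 and the first secondary hypothesis. The protocol says the study will be used to inform the sample size of a larger trial, so a shrunken estimate would carry over into that planning.

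**Working it through.** **1. Order of events.** Put together, the sections give: baseline survey, then allocation (Trial design); first arm-tailored counselling and EC kit at baseline (Behavioral counseling; Intervention arm); diary after the baseline assessment with arm-specific prompts (Tobacco product use), for 84 days post-baseline (Outcomes). The sentence "CPD at baseline and 12 weeks will be extracted from EMA data" can therefore refer only to diary days after allocation.

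**2. The plan's own power figures.** Inputs from Statistical methods: reductions of 5 (NRT) and 8 (EC) CC per day, or 5 and 9 with κ = 0.2. Sample size is 60 at 1:1, so n = 30 per arm. Two-sided alpha of 0.05 is my assumption. With SE = √(1/(n·m₁) + 1/(n·m₂) + 2κ/n):

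- 5 vs 8, κ = 0: SE = √(1/150 + 1/240) = 0.104; ln 1.60 = 0.470; 0.470/0.104 − 1.96 = 2.56; power 99.5%. The plan says greater than 90%.
- 5 vs 9, κ = 0.2: SE = √(1/150 + 1/270 + 0.4/30) = 0.154; ln 1.80 = 0.588; 0.588/0.154 − 1.96 = 1.86; power 96.8%. The plan says greater than 80%.

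Both figures reproduce, but they presume reductions measured from an untreated baseline.

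**3. Reduction measured from a late baseline (κ = 0).** If half of each arm's reduction has already happened in the baseline window, the measured reductions are 2.5 vs 4.0. SE = √(1/75 + 1/120) = 0.147, and power is 89.1%. If the early share is 20% on NRT and 50% on EC, they are 5 × 0.8 = 4.0 vs 8 × 0.5 = 4.0, a rate ratio of 1.0. These shares are illustrations.

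**4. Follow-up CPD adjusted for a late baseline.** Approximately,

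adjusted log ratio = true log ratio − slope × early log difference between arms.

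Assume a mean of 15 CPD before the trial (not in the protocol). Reductions of 5 and 8 then leave 10 and 7, a true ratio of 0.70 with log −0.357. With a quarter of the log effect present early and a slope of 0.98: −0.357 × (1 − 0.98 × 0.25) = −0.269, a ratio of 0.764.

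A simulation checked this. It used a Poisson model with log baseline covariate, a 7-day baseline window, between-person log-SD 0.45 and person-specific response log-SD 0.2 or 0.4. It had 100,000 per arm for bias and 400 runs at 30 per arm for power.

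| Share of log effect present early | Ratio, pre-randomisation baseline | Ratio, diary baseline | Power with diary baseline (response SD 0.2) |
|---|---|---|---|
| 0 | 0.70 | 0.70 | 0.91 |
| 0.25 | 0.70 | 0.76–0.77 | 0.78 |
| 0.50 | 0.70 | 0.84–0.85 | 0.48 |

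With the pre-randomisation baseline, power was 0.89 to 0.92 in these rows.

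A second simulation used 30 per arm, median CPD 15, a 7-day early mean, a 14-day week-12 mean, κ = 0.2 and 1,500 runs. It took early CPD as 80% of the pre-trial level on EC and 90% on NRT. The early log difference is ln(0.80/0.90) = −0.118, a third of −0.357. The adjusted ratio was 0.78.

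**5. The 24-week model.** The outcome is telephone self-report and the covariate is a diary value. An instrument difference common to both arms is absorbed by the intercept and slope, so it does not by itself bias the adjusted EC-versus-NRT contrast. It does distort within-arm change.

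**The case against.** The strongest reply is that the size of the problem is not established. The protocol does not say which diary days form the baseline, and the visits are by telephone with no stated delivery time for kits, so the first diary days could precede product use. The schedule (Fig. 1) is not reproduced in the text available here and might show a run-in. CPD is a secondary outcome, the effect aims are called exploratory, and the primary outcomes of feasibility and acceptability are untouched.

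Most of this stands as a limit on size and severity. It does not remove the contradiction: the text starts the diary after the baseline assessment, and arm-tailored counselling at baseline could change smoking even before a kit arrives.

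A reader might infer that adjustment must erase the effect. The documents do not support that. If the arms do not yet differ in the window, the bias is zero. Early CPD levels of 70% (EC) vs 90% (NRT), or 60% vs 85%, give adjusted ratios of 0.88 and 0.98. But ln(0.70/0.90) = −0.251 and ln(0.60/0.85) = −0.348 are about 70% and 98% of the week-12 log effect, already present in week one. Nothing in the protocol says that EC acts so fast, or faster than NRT. If NRT acted first, the bias would run the other way.

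It is also fair to object that a survey baseline is not free of problems. Set against a diary value at week 12, it mixes instruments in any within-arm reduction. The eligibility figure is CPD on smoking days only, and the minimisation factor is a two-level category; neither is an average daily CPD.

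**Conclusion.** The point holds in a conditional form. The plan names as baseline a measurement that its own text places after randomisation. Following it can bias the EC-versus-NRT estimate for CPD, to the extent that the arms already differ in the undefined baseline window, and it understates within-arm reduction to the extent that smoking has already fallen.

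For a true ratio of 0.70, the plausible range runs from no bias to an estimate of about 0.84 to 0.85 if half the log effect is present early. This rests on an assumed 7-day window, an assumed mean or median of 15 CPD and assumed early shares.

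The 24-week instrument change might be read as a bias in the randomised comparison; in the adjusted model it affects only within-arm change.

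This should be fixed before analysis because the result is meant to guide a larger trial. It does not touch the primary outcomes.

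**What to change.** In Statistical methods, replace the diary-based baseline with a continuous CPD value recorded in the baseline survey before randomisation. It should be the average per day over all days, not CPD on smoking days only and not the <20/≥20 category. Use it as the covariate in both the 12- and 24-week models, and keep EMA for the 12-week outcome.

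Report within-arm change on the same instrument at both times, for example survey against survey at 12 and 24 weeks, or label it as mixing instruments.

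If a diary run-in before allocation does exist, say so in Outcomes, Tobacco product use and Statistical methods, define its days, and use that window instead.

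The cost is a sentence or two. The baseline survey already covers smoking habits, but the protocol does not name average CPD as an item, so this must be confirmed. Recalled CPD is noisier than a diary, which costs a little precision but does not bias the randomised contrast.

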**Methods:**

In an open-label two-arm randomized controlled trial pilot study, 60 patients identified as smokers with a COPD diagnosis via electronic health records from a large urban health center are randomized in a 1:1 ratio to either standard care [counseling + nicotine replacement therapy (NRT)] or counseling + EC. The NRT arm will receive nicotine patches and nicotine lozenges for 12 weeks. The EC arm will receive EC for 12 weeks. Both cohorts will receive counseling from a licensed mental health counselor. Using ecological momentary assessment, participants will report their use of CC in both arms and EC use in the EC arm daily via text message. Primary outcomes will be feasibility and acceptability of intervention, and secondary outcomes will be reduction in CPD and change in COPD symptoms as measured by COPD Assessment Tool (CAT) score at 12-weeks. EC displacement of CC. To explore attitudes towards the use of EC as a harm-reduction strategy for patients with COPD, interviews will be performed with a sample of participants from both study arms.

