## Methods

In conjunction with a qualitative study using in-depth interviews with 20 study participants, the proposed study seeks to conduct an open-label randomized controlled trial (RCT) comparing the effect of standard care (NRT + counseling) to EC + counseling on reduction of CPD in 60 smokers with COPD. Specifically, this study aims to: (1) determine the feasibility and acceptability of an EC intervention for CC harm reduction among a COPD population; (2) estimate EC-related reduction in CPD 12 weeks post baseline; (3) measure engagement with the text-messaging-based smoking diary; and (4) estimate the effect of EC on reductions in COPD symptoms. Aims examining intervention effect are exploratory as the study is not powered to detect significant differences in results. The study protocol has been approved by the NYU Langone Institutional Review Board (IRB).

The primary hypothesis to be tested is: EC is a feasible and acceptable harm-reduction intervention among patients with COPD who smoke. Secondary hypotheses include: (1) An EC harm-reduction intervention will be more effective than NRT in reducing CPD in patients with COPD who smoke; and (2) An EC harm-reduction intervention will be more effective than NRT in reducing COPD symptoms in patients with COPD who smoke.

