#### Inclusion criteria

Potential participants will be included if they (1) have an ambulatory ICD-10 code for COPD in the last 12 months; (2) a COPD Assessment Tool (CAT) [27] score ≥ 10; (3) are aged 21 to 75 years (the legal age for purchasing EC is 21); (4) are a current CC smoker (more than 5 packs in a lifetime; smokes 4 or more days/week); (5) smoke at least 5 CC per day on days they smoke CC; (6) are motivated to quit smoking (at least a 5 on a 10-point Contemplation Ladder [28]); and (7) possess a phone with text messaging capabilities.

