### Trial design

After completing the baseline survey on tobacco use, physical health, and mental health, we will use a two-arm study design to randomize 60 patients to counseling + NRT (standard care) or counseling + EC. Participants will receive four counseling sessions in 12 weeks; each session will follow a study visit monitoring any physical or mental changes and side effects from using NRT or EC. All participants will complete a follow-up survey at 24 weeks (Fig. 1). During the 12 weeks of study participation, participants will report their tobacco use daily by responding to automated text messages serving as a smoking diary. We will also invite 20 participants for an in-depth interview on their study experience, outcome expectations, EC perceptions, and barriers to smoking cessation.

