This study is not meant to provide a definitive test of intervention efficacy and will be used to inform future sample sizes for a larger trial [48, 49]. In the primary analysis the sample size is anticipated to provide 80% power to detect a difference of 0.73 points in intervention satisfaction between study arms. For other primary measures, the sample size is anticipated to provide exploratory results to examine observed trends, but not statistically significant difference. For secondary analyses of effectiveness, in a Poisson generalized linear model for the number of CC reduced from baseline to follow-up, we will have greater than 90% power to detect a rate ratio of RR = 1.60 (e.g., a reduction by 5 CC per day in the NRT condition vs. 8 in the EC condition). If there is marked overdispersion of the number of CC per day reduced (κ = 0.2), we will still have greater than 80% power to detect RR = 1.80 (e.g., 5 vs. 9 CC per day reduction). Similarly, without considering covariates, we have 80% power to detect a difference of at least 2.7 on the CAT score, and with effective covariates, we have 80% power to detect a difference of 2.2. Translated to standardized mean differences, these are modest effects (d = 0.33 and d = 0.26). In secondary analyses, we will consider CPD collected daily over a 14-day period prior to the end of the 12-week follow-up. This will increase the power by increasing sample size providing for greater than 90% power to detect a rate ratio of RR = 1.20 (e.g., a reduction by 5 CC per day in the NRT condition vs. 6 in the EC condition). If there is marked overdispersion of the number of CC per day reduced (κ = 0.2), we will still have greater than 80% power to detect RR = 1.40 (e.g., 5 vs. 7 CC per day reduction).

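### The cigarettes-per-day power figures are for a Poisson model of the reduction, which is not a count and not the planned analysis, so they do not describe the comparison that will be run

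*Protocol article*

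**What the plan says.** In the protocol article, Statistical methods, the planned analysis of CPD is a Poisson or negative binomial regression "with follow-up CPD/CAT Score regressed on baseline CPD/CAT Score and an indicator variable of study condition". The response is the follow-up value, and the arm effect is a ratio of follow-up CPD.

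The power paragraph of the same section uses another response. It works "in a Poisson generalized linear model for the number of CC reduced from baseline to follow-up" and claims "greater than 90% power to detect a rate ratio of RR = 1.60 (e.g., a reduction by 5 CC per day in the NRT" arm against 8 in the EC arm. With κ = 0.2, described as marked overdispersion of the number reduced, it adds that "we will still have greater than 80% power to detect RR = 1.80 (e.g., 5 vs. 9 CC per day reduction"). Two further claims for a 14-day window, rate ratios of 1.20 (5 vs 6) and 1.40 (5 vs 7), are built in the same way.

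On baseline smoking the article gives only the entry rule that participants "smoke at least 5 CC per day on days they smoke CC" and minimisation strata split at 20 CPD. It states no baseline mean or SD. On the status of these aims, the opening of Methods says "the study is not powered to detect significant differences in results".

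**The concern.** There are two separate faults.

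First, the response in the power calculation cannot follow the distribution assumed for it. Baseline minus follow-up is negative for anyone who smokes more, and a Poisson likelihood does not admit negative values. It is also bounded above by baseline, so a participant who enters at 5 CPD cannot reduce by 8 or 9. The Poisson assumption also ties the between-person SD of the reduction to its mean, which need not be true of a difference of two measurements.

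Second, the model that was powered is not the model that will be fitted. A ratio of mean reductions and a ratio of follow-up means are different quantities, and the dispersion of a reduction is not the dispersion of follow-up CPD. A reader who takes the 90% and 80% figures as properties of the planned comparison would be misled. Because the pilot is meant to inform the sample size of a larger trial, an effect and a dispersion on the wrong scale could be carried forward.

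**Working it through.** **Inputs.** Total 60 ("we will use a two-arm study design to randomize 60 patients to counseling + NRT (standard care) or counseling + EC"), 1:1 allocation per the Abstract ("are randomized in a 1:1 ratio to either standard care"), so 30 per arm. Effects and κ come from the power paragraph. Assumed here: two-sided α = 0.05 (not stated), variance μ + κμ² (usual reading of κ), and no loss to follow-up.

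**Formula.** Wald test of a log rate ratio:
SE² = (1/μ₀ + κ)/30 + (1/μ₁ + κ)/30; power = Φ(|ln(μ₁/μ₀)|/SE − 1.96).

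**Step 1: the article's own figures, on its own model.**
- 5 vs 8, κ = 0: ln(8/5) = 0.470, SE = √[(0.200 + 0.125)/30] = 0.104, power 99.5%.
- 5 vs 9, κ = 0.2: ln(9/5) = 0.588, SE = √[(0.400 + 0.311)/30] = 0.154, power 96.8%.

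Both exceed the stated bounds. With 24 per arm (20% loss, assumed) they are 98.1% and 92.7%. The arithmetic is sound for the model named.

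**Step 2: what that model implies.** The SD of the reduction is √5 = 2.2 in the NRT arm and √8 = 2.8 in the EC arm under Poisson. With κ = 0.2 it is √(5 + 0.2·25) = 3.2 at mean 5 and √(9 + 0.2·81) = 5.0 at mean 9.

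**Step 3: the same absolute reductions on the planned scale.** If mean baseline is B, follow-up means are B − 5 against B − 8 or B − 9. B is an assumption. So is κ here: the article attaches it to the reduction, and below it is taken as the dispersion of follow-up CPD left after baseline adjustment. Each example keeps the overdispersion that the article gives it.

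| B | 5 vs 8, κ = 0: means, ratio, SE | Power | 5 vs 9, κ = 0.2: means, ratio, SE | Power |
|---|---|---|---|---|
| 12 | 7 vs 4, 0.57, 0.114 | 99.8% | 7 vs 3, 0.43, 0.171 | 99.9% |
| 15 | 10 vs 7, 0.70, 0.090 | 98% | 10 vs 6, 0.60, 0.149 | 93% |
| 20 | 15 vs 12, 0.80, 0.071 | 88% | 15 vs 11, 0.73, 0.136 | 62% |
| 25 | 20 vs 17, 0.85, 0.060 | 77% | 20 vs 16, 0.80, 0.131 | 40% |

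The 90% bound is crossed just above B = 19 (90.6% at 19) and the 80% bound just above B = 17 (81% at 17). No row has a ratio of 1.60 or 1.80, or its reciprocal (0.63 or 0.56), because the ratio depends on B.

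**Step 4: check by simulation.** Follow-up CPD was regressed on log baseline and arm in a Poisson GLM with robust standard errors, 500 runs per scenario. At B = 15 (baseline SD 8, assumed) and B = 20 (SD 10, assumed), 5 vs 8 with κ = 0 gave 97.6% and 90.2%; 5 vs 9 with κ = 0.2 gave 89.2% and 59.4%. These agree with the table within a few points. In the same runs 3% and 6% of participants had a negative reduction with κ = 0, and 9% and 15% with κ = 0.2.

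**Step 5: which fitted model.** If follow-up CPD has κ = 0.2 and a Poisson model is fitted with its model-based standard errors, the variance is understated by a factor 1 + κμ. The type I error is about 2[1 − Φ(1.96/√(1 + 0.2μ))]: 26% at a mean of 10, 29% at 12 and 33% at 15.

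**The case against.** A reader might infer that the stated power is simply too optimistic. The document does not support that. Its bounds follow from its inputs with room to spare, and on the planned scale they are still met when mean baseline is low and overdispersion is no greater than stated. With no baseline mean or SD given, neither optimism nor its absence can be shown. Lower figures follow if κ = 0.2 is added to the 5 vs 8 example (68% at B = 15), but the article claims no power for that combination.

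It can also be said that the reduction is only a loose name for the change outcome listed under Outcomes. The examples rule this out: 8/5 = 1.60 and 9/5 = 1.80 are ratios of reductions.

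On impact, CPD is a secondary outcome, the effect aims are called exploratory, the limitations paragraph restricts the disclaimer to small differences, and the article does not derive N = 60 from this calculation. All of that stands and limits the consequence, but it does not make the quoted power apply to the planned test.

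Finally, negative binomial is already one of the two planned options, and the rule for choosing may sit in an analysis plan that is not shown. The type I error figures therefore apply only if a Poisson fit with model-based standard errors is used; they do not show that the plan will use one.

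**Conclusion.** The point holds as a mismatch, and that part needs no assumption. The powered response is a signed, bounded difference rather than a count. The powered model is not the planned one, and the rate ratios of 1.60, 1.80, 1.20 and 1.40, with the κ attached to the reduction, are not parameters of the planned model.

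The size is conditional. With 30 per arm, two-sided 0.05 and κ read as residual dispersion of follow-up CPD, the 90% and 80% bounds carry over only if mean baseline is below about 19 and 17 CPD respectively. Above that, power falls to 77% and 40% at 25 CPD. The minimisation strata show that participants at 20 CPD or more are expected, but not what the mean will be. The importance is moderate: a stated figure needs correcting in an exploratory secondary analysis.

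**What to change.** Delete the model for the number of cigarettes reduced and its rate ratios, including the 14-day versions. In their place, state power or expected precision for follow-up CPD given baseline, and give the assumed baseline mean, control follow-up mean, dispersion of follow-up CPD and α.

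For example, with the control arm falling from 15 to 10 CPD and 30 per arm, 80% power corresponds to a follow-up ratio of about 0.66 at κ = 0.2 (|ln 0.66| = 0.416, SE = 0.147) or 0.56 at κ = 0.5 (|ln 0.56| = 0.580, SE = 0.206). The second κ is an illustrative assumption.

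Specify that the model will be negative binomial, or Poisson with robust or quasi-Poisson standard errors, so that a Poisson fit with model-based errors is not left open.

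The cost is wording and a recalculated figure, which may be less favourable than the present one. The design and data collection are unchanged.

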#### Randomization

After eligibility screening, participants will be randomized into one of the two study arms (EC or NRT; ratio 1:1) using minimization methodology. This approach has been found to achieve significantly better covariate balance than other randomization methods with a small sample size [30]. Randomization will be stratified by three key variables CAT score (10–19 and ≥ 20), CPD (< 20 and ≥ 20), and sex and will occur using a REDCap based system which includes verification of eligibility criteria prior to the assignment of a study ID and intervention group. Due to the nature of the study, participants are not blind to their randomization allocation.

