Our study protocol has a few limitations. First, as a pilot study the protocol is not powered to detect small differences in CPD or CAT Scores between the NRT and EC arms. Second, CAT Score is not the gold standard for the assessment of respiratory health. If this study is successful, future research needs to include assessment of airflow by spirometry, as well as by assessment of small airway function using respiratory oscillometry. While FEV1 change is not typically observable in early stage COPD patients, oscillometry may identify the presence of small airway injury in this population [72]. Adherence to study medications is not directly measured, therefore analyses are limited to intent-to-treat rather than per-protocol. The NJOY EC used in the study is not representative of all EC available and additional research using alternate products is called for. EC contain nicotine, which is an addictive substance and therefore there is potential for participants to continue EC use after the study is complete. The counseling protocol does not include EC cessation. Future research on EC cessation methods and continued EC use after switching is called for. Finally, all study measures are self-report. Future studies should include bio-confirmation of CC reduction such as CO.

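### The CAT power statement is internally inconsistent: with 30 per arm, 80% power needs d of about 0.74 unadjusted, not 0.33 or 0.26

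*Protocol article*

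**What the plan says.** The article fixes the sample under Trial design: "we will use a two-arm study design to randomize 60 patients to counseling + NRT (standard care) or counseling + EC". Under Randomization, allocation is 1:1: "participants will be randomized into one of the two study arms (EC or NRT; ratio 1:1) using minimization methodology". That is 30 per arm.

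Statistical methods then gives two power figures for the CAT score. The first is unadjusted: "without considering covariates, we have 80% power to detect a difference of at least 2.7 on the CAT score". The second, at the same power, lowers the detectable difference to 2.2 points when effective covariates are added. The next sentence converts both to a standardised scale: "Translated to standardized mean differences, these are modest effects", with d = 0.33 and d = 0.26 in brackets. No alpha, CAT standard deviation, covariate correlation or dropout rate is given.

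Elsewhere the tone is more cautious. The Methods opening, on the aims that examine intervention effect, says "the study is not powered to detect significant differences in results". The limitations in the Discussion say "the protocol is not powered to detect small differences in CPD or CAT Scores between the NRT and EC arms".

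**The concern.** A d of 0.33 or 0.26 is far below what two groups of 30 can usually detect with 80% power. The passage gives each effect both in CAT points and in SD units, so it implies an SD. At that SD, the sample size and the power cannot both be right.

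CAT change at 12 weeks is one of two named secondary outcomes, it carries a secondary hypothesis, and Statistical methods says the study will inform the size of a larger trial. If d = 0.33 were the real target, this trial would miss it about three times in four on an unadjusted comparison, and a null CAT result could be misread as evidence against such an effect. A later trial that took 30 per arm as enough for d = 0.33 would be nearly five times too small (145/30 = 4.8). If instead the points are right and d is wrong, readers are told that the trial can detect modest effects when it can detect only large ones.

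**Working it through.** **Inputs from the article.** 30 per arm; 80% power; 2.7 points and d = 0.33 without covariates; 2.2 points and d = 0.26 with them.

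**Assumed.** Two-sided alpha 0.05 and no dropout (which favours the plan). The same section offers some support for this alpha. Its claim of 80% power for a 0.73-point satisfaction difference reproduces at 30 per arm if the SD is 1 (also assumed): 0.73/√(2/30) − 1.96 = 2.827 − 1.96 = 0.867, so power is 81% (79% by the noncentral t).

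**1. Smallest d with 80% power.** (1.96 + 0.8416) × √(2/30) = 2.8016 × 0.2582 = 0.723. The noncentral t gives 0.736. The ratio to 0.33 is about 2.2.

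**2. Power at the stated d values.** Power = Φ(d/0.2582 − 1.96).
- d = 0.33: Φ(1.278 − 1.96) = Φ(−0.682) = 25%; noncentral t 24%.
- d = 0.26: Φ(1.007 − 1.96) = Φ(−0.953) = 17%; noncentral t 17%.
- d = 0.26 with the implied covariate gain: the stated differences imply that the residual SD shrinks by 2.2/2.7 = 0.815 (or 0.26/0.33 = 0.788 from the d values). The effective d is then 0.32 to 0.33, and power is 23% to 24%.

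So the plan's 80% does not reproduce.

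**3. Size needed for 80% power.** n per arm = 2 × 2.8016²/d² = 15.70/d².
- d = 0.33: 15.70/0.1089 = 144.2, so 145 per arm.
- d = 0.26: 15.70/0.0676 = 232.2, so 233 per arm with no covariate gain.

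**4. SD implied by the pairs.** 2.7/0.33 = 8.2 and 2.2/0.26 = 8.5. These agree within rounding, so both d values appear to use one unadjusted SD.

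**5. Which figure could be right?**

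| CAT SD | Basis | Detectable unadjusted difference (0.736 × SD) | d for 2.7 points |
|---|---|---|---|
| 3.7 | makes 2.7 points correct (2.7/0.736) | 2.7 | 0.73 |
| 5.8 | uniform spread over the eligible baseline range, 10 to 29 | 4.3 | 0.47 |
| 8.2 | implied by d = 0.33 | 6.0 | 0.33 |

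The first row has a plausible origin. The planned model is Poisson or negative binomial. A Poisson comparison of means 15 and 12.3 has standard error √(27.3/30) = 0.954, so power is Φ(2.7/0.954 − 1.96) = Φ(0.870) = 81%. The corresponding d is 2.7/√13.65 = 0.73.

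**6. Attempts to rescue d = 0.33.**
- One-sided tests at 30 per arm: 35% to 36% at 5%, 50% at 10%, 67% at 20%.
- 60 per arm instead of 60 in total: 44%.
- One-sided paired or one-sample test on all 60: 81%, but that is not a comparison between arms.
- Baseline adjustment with correlation r, detectable d = 0.736 × √(1 − r²): power at d = 0.33 is 31% (r = 0.5), about 43% (0.7), about 56% (0.8) and about 83% (0.9). To reach 80%, r must be about 0.89 for d = 0.33 and about 0.93 for d = 0.26.
- Averaging four follow-up scores with baseline adjustment: 80% at a common correlation of 0.8.

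The article states none of these. The covariate gain it does imply, 0.815, corresponds to r = √(1 − 0.815²) = 0.58.

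**The case against.** The strongest reply is that the benchmark is not the planned analysis. The base model regresses follow-up CAT on baseline CAT, so the figure without covariates might already be baseline-adjusted, with only further covariates left out. That reading is open. It means that 80% power at d = 0.33 is unsupported rather than strictly impossible. But it needs r near 0.9, which the article neither states nor hints at.

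Second, a reader might infer that 2.7 and 2.2 points are themselves too small by a factor of about 2.2. The article does not support that. It depends on an SD of 8.2, which the article never states and which comes only from the d values in dispute. With baseline CAT limited to 10 to 29, 8.2 also looks high at baseline, though follow-up scores may spread more widely. At an SD of about 3.7 the 2.7 points stand and the d values are the error.

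Third, CAT is a secondary outcome in a pilot that disclaims a definitive efficacy test, and the limitations speak of small differences where Statistical methods speaks of modest ones. This softens both the harm and the contradiction between sections. It does not make a specific power figure correct, and the study is offered as a basis for sizing the next trial.

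**Conclusion.** The inconsistency stands. With 30 per arm and a two-sided 5% test (assumed), 80% power requires d of about 0.74 unadjusted. At the stated d values power is about 24% (d = 0.33) and 17% (d = 0.26), or about 24% for the latter with the implied covariate gain in full. No one-sided level tried, nor doubling the sample to 60 per arm, restores 80% for a comparison between arms. Only strong, unstated correlations would.

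Which number is wrong cannot be settled from the article. Over SDs of 3.7 to 8.2 the unadjusted detectable difference runs from 2.7 to 6.0 points, so the shortfall in points lies anywhere from none to a factor of 2.2. Dropout would make every figure worse: with 24 evaluable per arm (assumed) the detectable d rises to 0.83.

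**What to change.** In Statistical methods:

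- Remove the claim of 80% power at d = 0.33 and d = 0.26, and the description of these effects as modest.
- State the alpha and sidedness, the CAT SD, the baseline correlation r, and whether the figure without covariates already adjusts for baseline. If a Poisson calculation was used, give the comparator mean.
- Restate the detectable effect for 30 per arm as d of about 0.74 unadjusted, or 0.74 × √(1 − r²) with baseline adjustment. Derive the point differences by multiplying by the stated SD.
- Do not insert 8.2 as the SD, or 6.0 points as the detectable difference, unless the sponsor confirms that SD from its own source.
- Bring the text into line with the limitations in the Discussion, which say that small CAT differences are not powered.

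The cost is wording only. Sample size, conduct and analysis are unchanged. The stated figure becomes less favourable.
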